### Primary outcome

2.9

The primary outcome will be self-reported burnout, as measured by the OLBI, with the primary endpoint being 3 months post-treatment.

### Secondary outcomes

2.10

The secondary outcomes will be.•burnout (OLBI) at post-treatment•self-reported anxiety, depression, and stress (DASS-21) at post-treatment and 3 months post-treatment;•psychosocial functioning (WSAS) at post-treatment and 3 months post-treatment;•workforce participation (WHO-HPQ) at post-treatment and 3 months post-treatment;•workforce attrition intentions (TIS-6) at post-treatment and 3 months post-treatment;•service acceptability (CSQ-8) at post-treatment.

### Treatment fidelity and service usage

2.11

To assess fidelity of telehealth sessions in the blended care arm, the treating clinical psychologist will complete a survey after each session answering 3 questions [1]: *“Which topics from the clinical manual were covered in this session?“*, recorded as a single item response to a list of the available Navigating Burnout modules [2]; *“How closely did you follow the suggested structure for Topic X?”* where “X” refers to the module selected in question one, recorded as a single item response to a list of three options of “Not at all”, “Mostly” or “Completely”; and [3] *“Did the session identify any participant risks that require escalation?“*, recorded as a single item response to two options of “Yes” or “No”. Clinicians were also offered an optional free text field to record any session details they deemed relevant to treatment fidelity. Quantitative data will be analysed to assess protocol coverage, protocol adherence, and risk frequency. Qualitative data will be reviewed for additional threats to fidelity.

Navigating Burnout and Black Dog Institute website analytics are recorded automatically by the SAS CI360 platform for service evaluation purposes. As Navigating Burnout is publicly available without registration, participants in the self-guided arm will be provided with a unique link to Navigating Burnout containing their record ID on REDCap (e.g. www.blackdoginstitute.org.au/the-essential-network/burnout/[ID]). SAS CI360 will then be used to export all website analytics (e.g. time of access, pages visited) containing this unique record ID identifier and the Navigating Burnout pages visited during this session. These sessions will then be linked to individual participants’ data on REDCap using the associated URL record ID in order to objectively examine service usage.

In the active attention control, fortnightly emails containing links to digital self-care psychoeducation materials will be disseminated through Campaign Monitor – electronic direct mail software. Campaign Monitor automatically records when participants open an email, allowing for a measure of service usage in the active attention control arm.

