### Interventions

2.3

Navigating Burnout is a digital psychotherapeutic program that includes intervention components derived from evidence-based cognitive-behavioural and acceptance and commitment therapies that are delivered across seven topics [1]: understanding burnout [2]; increasing social connections [3]; managing unrealistic expectations [4]; setting limits [5]; valued living [6]; self-care; and [7] a module for managers detailing evidence-based strategies for improving workplace mental health (see Fig. 2). Each topic contains lived experience videos, behavioural strategies, and CBT worksheets.

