**Fig. 2 fig2:**
[figure not shown]
Example screenshot from Navigating Burnout.

In the blended care arm, a clinical psychologist from the BDI Clinical Service will work through the Navigating Burnout content with participants over 10 weeks in five fortnightly 1-hour consultations. Clinical psychologists will follow a treatment manual mirroring the content of Navigating Burnout, with guidance on integrating digital content into session activities. Session 1 covers understanding burnout and self-care, session 2 covers unrealistic expectations, session 3 covers setting limits, session 4 covers valued living, and session 5 covers increasing social connections and information for managers. Session 1 is fixed and the same for all participants, whereas sessions 2–5 occur in an order determined by the participant and their clinical psychologist. Clinical psychologists will be offered a training program comprising [1]: a comprehensive treatment manual summarising the study protocol, the digital content, and session plans with suggested approaches to delivering the program's CBT strategies [2]; a 90-min protocol training session delivered by PB covering the design and purpose of the study, how to use the training manual, how to embed the digital content in a standard telehealth consultation, and roleplays of case examples; and [3] optional monthly 60-min clinical supervision sessions with PB. Clinicians will have discretion to tailor consultations to participant needs as long as (a) the clinical focus remains burnout; and (b) the program content is delivered in full across the five consultations. Participants will also have independent access to the digital version of Navigating Burnout over the 10 weeks between consultations and be directed by their clinical psychologist to specific components of the program in order to support awareness and management of burnout. During the 10-week treatment period, clinical psychologists providing care in the blended arm will provide immediate risk assessment and intervention for any participant expressing intent to self-harm or suicide and report any concerns related to suicide or self-harm attempts to PB.

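### The blended-arm fidelity form takes one module per session although sessions 1 and 5 each cover two, so on the likelier reading at most five of seven topics can be recorded

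*Protocol article*

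**What the plan says.** Protocol article, section 2.3 (Interventions): the program is "delivered across seven topics". In the blended arm these are worked through in "five fortnightly 1-hour consultations". The session plan pairs topics at both ends: "Session 1 covers understanding burnout and self-care", and "session 5 covers increasing social connections and information for managers". Sessions 2, 3 and 4 take one topic each. Clinicians may tailor the consultations provided that burnout stays the focus and "the program content is delivered in full across the five consultations".

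Section 2.11 (Treatment fidelity and service usage): the psychologist completes a three-question survey after each session. Question 1 asks, in the plural, which topics were covered, but the answer is "recorded as a single item response to a list of the available Navigating Burnout modules". Question 2 asks how closely the suggested structure was followed for the module chosen in question 1, on three options. Question 3 is a yes/no item on risk. An optional free-text field is offered. The quantitative answers are to be analysed for coverage, adherence and risk frequency, and the qualitative answers reviewed for further threats to fidelity.

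On digital use, the same section says that "participants in the self-guided arm will be provided with a unique link to Navigating Burnout", carrying a record ID that lets website analytics be tied to the person. For the control arm it describes tracking of email opens. Table 1 lists objective service usage at both follow-ups without naming arms.

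**The concern.** The form and the session plan come from the same article and do not match. A clinician who delivers session 1 as planned has two topics to report and, as the form is described, one place to report them. The same happens in session 5. The shortfall is not random: it always falls on the two double-topic sessions, that is, on understanding burnout or self-care, and on social connections or the managers' material.

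The survey is the only structured check the article describes on whether blended content was delivered in full. If a session that dropped self-care leaves the same structured record as one that delivered both topics, the check cannot do its job. Section 2.12 bases the sample size on blended against self-guided care. Knowing whether blended care was delivered as designed therefore helps in reading that comparison, particularly if it shows no difference.

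**Working it through.** No sample-size or error-rate formula applies; the check is a count.

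**Inputs**
- Topics in the program: 7 (section 2.3).
- Sessions in the blended arm: 5 (section 2.3).
- Topics per session, sessions 1 to 5: 2, 1, 1, 1, 2 (section 2.3).
- Forms per session: 1 (section 2.11).
- Modules recorded per form: 1, if question 1 is pick-one (section 2.11).

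**Step 1: reproduce the plan's own figure.** 2 + 1 + 1 + 1 + 2 = 7. Each topic appears once, so the session plan is consistent with the stated seven topics and with full delivery.

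**Step 2: ceiling of the structured record.** Maximum recordable topics = sessions × forms per session × modules per form = 5 × 1 × 1 = 5. As a share of the topics, 5/7 = 71.4%. The shortfall is 7 − 5 = 2 topics, or 2/7 = 28.6%. Sessions 2 to 5 may be taken in any order, but this does not change the count.

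**Step 3: can the form tell full from partial delivery?** Suppose one participant receives all 7 topics, and another receives 5 because one topic was dropped from session 1 and one from session 5. Both can yield the same five module entries. The structured items cannot separate 7/7 delivered from 5/7 delivered.

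**Step 4: dependence on how the items are read**

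| Reading of the form | Most topics with a coverage record | Most topics with an adherence rating |
|---|---|---|
| Question 1 pick-one, question 2 once | 5 of 7 (71%) | 5 of 7 (71%) |
| Question 1 accepts several, question 2 once | 7 of 7 | 5 of 7 (71%) |
| Question 1 accepts several, question 2 repeated per topic | 7 of 7 | 7 of 7 |

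Two features of section 2.11 favour the first row. The response-format phrase used for question 1 is also used for questions 2 and 3, which are plainly pick-one. And question 2 refers back to a single module. The plural in question 1 points the other way.

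**Step 5: objective digital usage by arm, as described in section 2.11.** Self-guided: ID-tagged link. Control: email opens. Blended: no method described, although section 2.3 gives these participants independent access to the same site.

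**The case against.** The survey itself is not shown, and the article paraphrases it. The response-format phrase could mean one survey item answered from a list with several ticks allowed, and the placeholder topic in question 2 is compatible with repeating that question. This stands as far as it goes: the 71% is conditional on the pick-one reading. It does not remove the point, because the plural question and the single-module follow-up still disagree, and even with a multi-select question 1 the adherence gap remains unless question 2 is repeated.

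The article also does not define coverage as distinct topics out of seven. Scored by session, a fully delivered course would show 5/5. That is fair, and a reader should not infer that the trial will necessarily report perfect delivery as incomplete. But a per-session score would not show whether all seven topics were delivered, which is what the condition in section 2.3 requires.

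The free-text field allows a second or an omitted topic to be noted. It is optional and reviewed qualitatively, so it is a partial remedy that leaves the quantitative limit in place.

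On digital usage, a reader might infer that blended participants are excluded from tracking, or that use cannot be compared between the two arms. The article supports neither. It says that self-guided participants get a unique link, not that others do not, and Table 1 does not restrict objective usage by arm. Sections 2.8 and Table 1 also provide for self-reported usage at follow-up. What can be said is that no objective method is described for the blended arm.

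Finally, fidelity is not among the primary or secondary outcomes in sections 2.9 and 2.10, the analysis in section 2.13 is by intention to treat, and no stated analysis is conditioned on coverage, adherence or usage.

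**Conclusion.** The point holds as a mismatch between the fidelity form in section 2.11 and the session plan in section 2.3. This is not missing detail: the article states both the response format and the session plan. On the pick-one reading, and counting against seven topics, two topics per fully treated participant have no coverage or adherence record.

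The reach is limited to fidelity data in one arm. It would be tempting to read this as a threat to the blended versus self-guided result. The documents do not support that: the primary analysis and the sample size do not use these data. What suffers is the ability to document that blended care was delivered as designed.

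The undescribed objective usage method for the blended arm is a secondary point, and the main one stands without it. It should be corrected, but it is not a reason to hold the trial.

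**What to change.** 1. Let question 1 accept every topic covered in the session, and repeat question 2 for each topic ticked. The ceiling then becomes 2 + 1 + 1 + 1 + 2 = 7 of 7 for both coverage and adherence.
2. State that coverage is the number of distinct topics covered out of seven across the five sessions.
3. If the live form already works this way, leave it alone and correct the description in section 2.11.
4. Issue the same ID-tagged links to blended participants, or state the method used for that arm. This would allow an objective comparison of digital use alongside the self-reported usage already collected.

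The cost is a change to one survey form and the reuse of one link template, plus a few seconds of clinician time after the two double-topic sessions. For sessions already recorded on a pick-one form, the second topic may not be recoverable reliably, so the change is worth making early. Any such sessions should be identified when coverage is reported.

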### Sample size

2.12

We will enrol 207 participants to complete the trial. This sample size is sufficient to examine the primary outcome using repeated measures ANOVA of whether the blended care version of the Navigating Burnout program leads to significantly lower burnout between baseline and 3 months post-intervention compared to self-guided treatment based on a power analysis (α = .05 and power = 0.80) using a conservative medium effect size of f = 0.25 between groups estimating a sample size of 53 per arm (WebPower). As there is limited literature on the effect of blended care treatments for burnout relative to self-guided digital psychotherapeutic programs, a medium effect size of f = 0.25 was chosen as a minimum clinically meaningful effect [28]. Accounting for a conservative estimate of 30% attrition based on previous research health professionals [19], 69 participants are required in each arm leading to a total sample size of 207.

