### Trial design

2.1

We will conduct a three-arm RCT to compare the effectiveness, acceptability, and cost-effectiveness of Navigating Burnout in reducing burnout among doctors across three delivery modalities.

Medical doctors (n = 207) will be randomly allocated to receive either [1] a blended version of the program combining the digital Navigating Burnout resources with five fortnightly telehealth sessions with a clinical psychologist [2]; a digital-only, self-guided version of the Navigating Burnout program; or [3] an active attention control where participants will be provided with digital self-care psychoeducation via email each fortnight. Across all conditions the treatment phase across will last 10 weeks.

We will measure self-reported burnout, psychosocial wellbeing, workforce engagement, and workforce attrition intentions before treatment, immediately after treatment, and 3 months after completing treatment (see Fig. 1 for trial design). This design will enable us to examine the effectiveness and acceptability of blended care Navigating Burnout compared to self-guided Navigating Burnout, as well as to examine the effectiveness of self-guided Navigating Burnout relative to an appropriate control.

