### Statistical methods

2.13

Study analyses will follow an intention-to-treat analysis plan using multiple imputation to account for missing data. To understand baseline variation and ensure experimental rigor, baseline scores on all psychosocial and occupational outcomes will be checked for between arm consistency using one-way analysis of variances (ANOVAs).

For the primary outcome (changes in OLBI burnout scores), between group variations (i.e., reductions in burnout between arms) will be examined using a 3 (blended, self-guided, active attention control) x 2 (baseline, 3 months post-treatment) mixed model ANCOVA controlling for gender, age, profession, and regionality and explored with pairwise comparisons. Identically formatted mixed model ANCOVAs will be used to analyse the secondary aims and outcomes of between arm and baseline to post-treatment and 3-month post-treatment differences in DASS (anxiety and depression), WSAS (psychosocial functioning), WHO-HPQ (workplace participation), and TIS-6 (attrition intention). The secondary aim and outcomes of comparing service acceptability between arms will be analysed using one-way ANOVAs.

If primary outcome data (i.e. OLBI at 3 months post-treatment) is unavailable for more than 5% of participants from the intention-to-treat population then exploratory and sensitivity analyses will be conducted. The following exploratory analyses of missing primary outcome data will be conducted to inform missingness categorisation and missing data handling: comparing proportion of attrition between arms, reasons for withdrawal, and baseline characteristics between those with and without the primary outcome. Best-worst and worst-best case sensitivity analyses will also be conducted alongside sensitivity analyses using last observation carried forward. Based on the results of these exploratory and sensitivity analyses, either complete case analysis or multiple imputation with 100 imputed data sets of the primary outcome will be conducted.

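### The 53 per arm is the three-group omnibus figure; on the same inputs the blended versus self-guided comparison it is said to power has about 72% power, not 80%

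*Protocol article*

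**What the plan says.** Section 2.12 opens with a sufficiency claim: "This sample size is sufficient to examine the primary outcome using repeated measures ANOVA". The question it attaches to that claim is whether blended care "leads to significantly lower burnout between baseline and 3 months post-intervention compared to self-guided treatment". That is a comparison of two arms.

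The inputs follow: "based on a power analysis (α = .05 and power = 0.80"), "using a conservative medium effect size of f = 0.25 between groups". The result is given as "between groups estimating a sample size of 53 per arm (WebPower"), raised to 69 per arm (207 in all) for 30% attrition. The section ties the effect size to the same pair of arms. It cites the limited literature on blended relative to self-guided care, and on that ground "a medium effect size of f = 0.25 was chosen as a minimum clinically meaningful effect".

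Section 2.13 analyses the primary outcome with a mixed ANCOVA of three arms by two time points, adjusted for gender, age, profession and regionality, "and explored with pairwise comparisons". Section 2.1 gives the comparison of blended with self-guided care as one purpose of the design, "as well as to examine the effectiveness of self-guided Navigating Burnout relative to an appropriate control".

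**The concern.** The power statement and the calculation appear to answer different questions. The text names a contrast with one degree of freedom. The number fits a test with two degrees of freedom, whose null hypothesis is that all three arms are equal. A significant result from that test could come entirely from blended care against control, and it would leave open whether adding a psychologist to the digital program helps.

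The consequence is in how the result is read. If blended care does not differ significantly from self-guided care, readers will take it as the outcome of a test with 80% power at the smallest effect the sponsor considers meaningful. If the true power is nearer 70%, that reading gives the null result too much weight.

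**Working it through.** **Inputs from 2.12 and 2.6.** f = 0.25, alpha = .05, power = 0.80, repeated measures ANOVA, 53 per arm, 30% attrition, 69 enrolled per arm, 1:1:1 allocation. Sidedness is not stated, but an F test is non-directional.

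**Formula.** I assume the usual non-central F form: numerator df = k − 1, denominator df = N − k, non-centrality λ = N·f². With two time points, the between-group and group-by-time tests give the same N in this form.

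**1. Reproduce the protocol's figure.** With k = 3:
- N = 157 gives power 0.799 and N = 158 gives 0.802, so N = 158 is needed.
- 158/3 = 52.7, rounded up to **53 per arm**. At N = 159 the power is 0.805.

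This matches the stated figure exactly.

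**2. Same inputs for the comparison named in the text.** With k = 2, f = 0.25 is d = 2f = 0.50.
- N = 127 gives 0.798 and N = 128 gives 0.801, so 128/2 = **64 per arm**.
- At 53 per arm: λ = 106 × 0.0625 = 6.625, power **72.2%** (72.5% with the error df pooled over three arms).

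**3. After the planned attrition.**
- 53 × 1.3 = 68.9, rounded to 69, which is the protocol's number.
- 69 × 0.7 = 48.3, so about 48 per arm have data.
- λ = 96 × 0.0625 = 6.0, power **67.9%** (68.2% pooled). The detectable d at 80% power is about 0.58.
- Keeping 53 with data would take 53/0.7 = 75.7, i.e. 76 per arm.

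The step from 72% to 68% therefore comes from the inflation method, not from the number of groups.

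**4. Other routes to 53.** A one-sided two-group t test needs 51 per arm (82% power at 53). A two-group between-factor formula that uses a correlation between time points gives 53 if that correlation is 0.65. The protocol states neither a one-sided test nor a correlation. Only the three-group F test gives 53 from the inputs as written.

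**5. Sensitivity to the correlation r between baseline and 3 months.** The protocol gives no r. If d = 0.50 is in raw outcome SDs (an assumption), the group-by-time test is a test of change, with effect 0.50/√(2(1 − r)):

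| r | Effect on change scale | Power at 53 | Power at 48 |
|---|---|---|---|
| 0.4 | 0.456 | 64% | 60% |
| 0.5 | 0.500 | 72% | 68% |
| 0.6 | 0.559 | 81% | 77% |
| 0.7 | 0.645 | 91% | 88% |

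If f = 0.25 is already on the scale tested, step 2 applies as it stands.

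**The case against.** The strongest defence is that the calculation suits the analysis. The primary model in 2.13 has three arms, and 53 per arm gives its omnibus test about 80% power. This is true, and it makes the fault a mislabelled claim rather than a sample size with no basis. It does not rescue 2.12, which attributes that power to one contrast.

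The second defence is that 72% and 68% are unadjusted figures, while the model uses baseline data. This stands in part. With r of 0.6 or 0.7 the change test at 53 per arm reaches 80%. If baseline OLBI were a covariate, the effect would be 0.50/√(1 − r²), giving 84% at 53 and 80% at 48 for r = 0.5. But 2.12 states no correlation and claims no such gain, and baseline OLBI is not among the covariates listed in 2.13. With r of 0.5 or less, the change test gains nothing.

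Three stronger readings are tempting, and the documents do not support them:
- **Inflated familywise error.** A reader might infer that the pairwise tests are run ungated and unadjusted. Section 2.13 does not say so. Its wording fits follow-up after an omnibus test, and gating or adjustment may be settled in an analysis plan that is not shown.
- **Power far below 68%.** A reader might treat f = 0.25 as the spread over three arms. Power for the pair would then depend on the assumed pattern of means: at 48 per arm, from about 32% to 84% over three simple patterns. The protocol specifies no pattern, and 2.12 justifies f by blended relative to self-guided care.
- **No primary question.** Section 2.13 alone does not rank the contrasts, but 2.12 names blended against self-guided, and the abstract and the Results section state the expected ordering.

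**Conclusion.** The point holds as an error in what 2.12 states. The figure of 53 per arm comes from a three-group omnibus test and does not give 80% power for blended versus self-guided care on the stated inputs. That comparison needs 64 per arm with data. It has about 72% power at 53, a shortfall of about 8 points that belongs to the group-number mismatch. It has about 68% at the 48 expected to remain, and the further 4 points belong to the attrition inflation. At 48 per arm the effect detectable with 80% power is about d = 0.58, larger than the 0.50 that the protocol treats as the smallest meaningful effect.

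This rests on f = 0.25 being the effect for that pair on the scale tested, a two-sided .05 test, and no gain from imputing missing outcomes. If d = 0.50 is in raw outcome SDs, power at 48 per arm runs from about 60% (r = 0.4) to 88% (r = 0.7). The shortfall is therefore not certain in practice, but the 80% is not supported by anything the protocol states.

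**What to change.** **Section 2.12.** Label 53 per arm as the three-group omnibus figure. Then do one of two things:
- state the power for blended versus self-guided care: 72% at 53 per arm, 68% at 48 completers per arm, detectable d about 0.58 at 80% power with 48, each with its assumptions (d = 0.50 on the scale tested, two-sided .05); or
- state and justify the correlation between baseline and follow-up that would bring the contrast to 80%, and say which model uses it.

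**Section 2.13.** Name the blended minus self-guided difference in OLBI at 3 months post-treatment as the primary 1-df contrast, so that the primary test answers the question in 2.12. The other pairwise comparisons follow it.

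**Cost.** Wording in two sections and no extra participants. The stated power becomes less favourable. For reference, holding 80% on the stated inputs alone would take 64 per arm with data, i.e. 64/0.7 = 91.4, so 92 enrolled per arm and 276 in all. The correction proposed here does not depend on that increase.

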**Methods:**

Doctors (n = 207) with burnout will be randomised to (1) a blended version of Navigating Burnout combining digital resources with five fortnightly telehealth sessions with a clinical psychologist, (2) a digital-only version of Navigating Burnout, or (3) self-care psychoeducation as an active attention control. Burnout, psychosocial wellbeing, workforce engagement and attrition, and service acceptability will be measured at baseline, post-treatment, and 3 months post-treatment.

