### Randomisation

2.6

Eligible participants will be randomly allocated to the blended care, self-guided, or active attention control arm using a 1:1:1 ratio. Randomisation will be completed following completion of baseline outcomes.

A randomisation list in a Microsoft Excel file will be prepared in advance using a random number generator using block sizes of 6, 9, and 12. When a participant is ready to be randomised, the list holder will be contacted, and the allocation provided. Participants will be informed which treatment they have been randomly assigned via email.

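### The 30% attrition allowance multiplies 53 by 1.3 instead of dividing by 0.7, so 69 per arm leaves about 48 completers and about 76% power, not 53 and 80%

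*Protocol article*

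**What the plan says.** The sample size paragraph (Protocol article, section 2.12) works in two steps.

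- **Before attrition.** With a 5% significance level, 80% power and a between-group Cohen's f of 0.25, the software calculation ends in "estimating a sample size of 53 per arm (WebPower").
- **After attrition.** "Accounting for a conservative estimate of 30% attrition based on previous research health professionals [19], 69 participants are required in each arm", and the sentence ends with a total of 207.

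Allocation is equal across the three arms (section 2.6: "using a 1:1:1 ratio"). The total of 207 is repeated in the abstract and in section 2.1. No other retention figure or inflation rule appears in the article.

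**The concern.** An attrition rate applies to the people enrolled, not to the people who remain. To end with a required number of completers, that number is divided by the expected retention. Adding 30% to the required number gives too few, because the 30% loss is then taken from the larger enrolled figure. The 69 looks like the result of that shortcut.

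If so, the trial fails its own calculation under its own assumption. The article tells readers that 207 is enough for 80% power on the primary outcome with 30% lost. A null result would then be read as coming from a trial with more power than it had.

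**Working it through.** **Inputs, all from section 2.12 unless noted**

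- α = 0.05, power = 0.80, Cohen's f = 0.25 between groups
- 53 per arm before attrition
- 30% attrition
- 69 per arm, 207 in total
- three arms, equal allocation (sections 2.6 and 2.13)

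**Step 1. Reproduce the 53.** The article does not say exactly how the software was set up, so this is a reconstruction. For a three-group F test, df₁ = 2, df₂ = N − 3 and the noncentrality is λ = f²N.

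- The smallest N with power of at least 0.80 is 158, which is 52.7 per arm, rounded up to 53.
- At N = 3 × 53 = 159: λ = 0.0625 × 159 = 9.94 and power = 0.805.

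The 53 therefore reproduces as a three-group test, with no credit for the correlation between baseline and follow-up.

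**Step 2. Reproduce the 69.**

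- 53 × (1 + 0.30) = 68.9, rounded up to 69. This matches.
- 53 / (1 − 0.30) = 75.7, rounded up to 76. This does not match.

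**Step 3. The allowance done correctly.**

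- 76 per arm × 3 = 228 in total; 228 − 207 = 21 short.
- Check: 76 × 0.70 = 53.2 completers per arm.

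**Step 4. What 69 per arm delivers at 30% loss.**

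- 69 × 0.70 = 48.3 per arm; 207 × 0.70 = 144.9 in total, against 159 required.
- Shortfall with 48 completers: (53 − 48)/53 = 9%.

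| Completers | λ = 0.0625 × N | Power, three-group F test |
|---|---|---|
| 159 (53 per arm) | 9.94 | 0.805 |
| 145 in total | 9.06 | 0.764 |
| 144 (48 per arm) | 9.00 | 0.761 |

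**Step 5. Attrition that 69 per arm can bear.** 1 − 53/69 = 16/69 = 23.2%. At 20% loss, 69 × 0.80 = 55.2 remain, which is enough. At 25%, 69 × 0.75 = 51.75 remain, which is not.

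**The case against.** **Imputation may recover some of the loss.** This is the strongest point. Section 2.13 opens with an intention-to-treat analysis using multiple imputation, and section 2.6 places randomisation after the baseline outcomes, so every randomised participant has a baseline burnout score. If data are missing at random, imputing from baseline brings the dropouts' baseline scores into an estimate of change. With equal variances and baseline-to-follow-up correlation r, the effective number per arm for mean change is about 2 / [(1 + r)/48 + (1 − r)/69]. The article gives no correlation, so r is an assumption here:

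| Assumed r | Effective n per arm | Power on the same F test |
|---|---|---|
| 0.3 | 53.7 | 0.81 |
| 0.5 | 52.0 | 0.80 |
| 0.7 | 50.3 | 0.78 |

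It is therefore too strong to say that imputation recovers nothing, and the 76% should be read as the complete-case figure. The rest of the objection does not carry. The gain depends on missingness at random and on r, and it reaches 53 only toward the low end of that range. Section 2.12 takes no credit for it and treats those lost as lost. Section 2.13 also leaves complete-case analysis open as the final choice. None of this makes 69 the right inflation of 53.

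**The 30% is described as conservative.** Actual loss may be lower, and up to 23.2% the 53 is kept. That is fair, and it is why the shortfall is stated at the assumed rate. But 30% is the rate that the article claims to have covered.

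**Four points of power is little.** It is modest, and no estimate, test or error rate changes. What is wrong is a stated figure for the primary outcome, and correcting it is cheap.

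**The power figures rest on a reconstruction.** This is true of the 80.5% and 76.1%. The error of 69 against 76 needs only the 53 and the 30% printed in section 2.12.

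**Conclusion.** The concern holds. The attrition step in section 2.12 is an arithmetic error: 30% attrition on a requirement of 53 per arm calls for 76 per arm (228), not 69 (207). At the assumed loss, the trial would end with about 48 per arm, 9% below its own requirement.

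On the three-group F test with f = 0.25 and complete cases, power would be about 76% in place of the stated 80%. That figure assumes that the reconstruction of the 53 is right and takes no credit for imputation or baseline correlation, just as the article takes none. The completer shortfall and the 23.2% limit depend on neither.

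**What to change.** Correct the attrition sentence in section 2.12 in one of two ways.

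1. State that 53/(1 − 0.30) gives 76 per arm, 228 in total, and enrol that number (21 more than planned).
2. Keep 207 and state what it supports: 53 completers per arm if attrition is at most about 23%, or about 48 per arm with about 76% power for the test used if attrition reaches 30%.

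If credit is to be taken for imputation or baseline adjustment, state the assumed correlation and show the resulting power.

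The second option is a change of wording only. It costs a slightly less favourable power statement and no recruitment. Under the first option, the 207 in the abstract and section 2.1 must change as well. Any other trial document that repeats the 80% power claim at 30% attrition should be brought into line.
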